**Fig. 1 Fig1:**
[figure not shown]
Schematic diagram of experimental protocol. PA, physical activity monitoring via actigraphy. D_2_O, heavy water ingestion period. BLG, β-lactoglobulin supplementation, at 23 g three times per day. PLA, placebo supplementation, energy matched to the β-lactoglobulin supplement. Strength, isometric and isokinetic contractions assessed via isokinetic dynamometry

### Participants

To address the study objectives, a cohort of 24 healthy young (18–45 years) males and females who satisfy the inclusion and exclusion criteria outlined in Table 1 will be recruited for this trial. Eligibility will be determined using a series of self-report questionnaires and a 3-day weighed food diary to assess baseline dietary protein intake. Volunteers that report a baseline protein intake in excess of 1.2 g·kgBM^−1^·day^−1^ will be deemed ineligible for participation in this study. The protocol for this study has received ethical approval from King’s College London Research Committee (reference: HR/DP-21/22-29290) and will be conducted in accordance with the Human Tissue Act and the Declaration of Helsinki and has been registered at clinicaltrials.gov under reference number NCT05496452 (version: 1, date: 15 December 2022). Participants will be reimbursed £500 for their time invested in the study.

**Table 1 Tab1:** Inclusion and exclusion criteria

**Inclusion**	**Exclusion**
1. Male and female	1. Dairy allergy or intolerance
2. Aged 18–45 years	2. Lower limb injury or surgery in the last 6 months
3. Healthy	3. Lower limb osteoarthritis or other musculoskeletal disorder
4. Physically active (≥ 150–300 min of moderate-intensity aerobic physical activity per week OR 75–150 min of vigorous-intensity aerobic physical activity per week)	4. A musculoskeletal or blood blotting disorder
5. Eumenorrheic and not taking any hormonal birth control (females)	5. An allergy to local anaesthetic
	6. Currently pregnant
	7. Current use of blood thinning medications
	8. Volunteers that take part in structured resistance exercise training
	9. Taking supplements considered to be anabolic to skeletal muscle (protein supplements, creatine, or omega-3 supplements)
	10. Consuming more than 1.2 g of protein per kilogramme of body mass per day in their habitual diet
	11. Volunteers involved in other studies at the time of enrolment
	12. Volunteers who have taken part in a tracer study in the past 18 months
	13. If without an understanding of verbal or written English
	14. Volunteers with a history of eating disorders

#### Power calculation

The sample size for this study has been estimated using an a priori power analysis of a previously published study by Kilroe et al. [19] that utilised the same unilateral leg immobilisation protocol, primary endpoint measurement (free-living integrated MPS rates assessed by deuterium oxide tracer methodology) and participant characteristics (healthy young adults). We calculated an effect size (d) of 1.6 for the primary endpoint (MPS) using Eq. 1.1$$\mathbf d\boldsymbol=\boldsymbol(\mathbf\mu\mathbf1\boldsymbol-\mathbf\mu\mathbf2\boldsymbol)\boldsymbol/\mathbf{SD}$$where μ1 is the mean value for muscle protein synthesis in group 1, μ2 is the mean value for muscle protein synthesis in group 2 and SD is the pooled standard deviation.

This effect size was entered into G*Power (version 3.1.9.2), with power set to 0.8 and significance level (*α*) set to 0.05. The required sample size was projected to be 12 per group, for a total of 24 participants. Hence, we plan to recruit 24 healthy, young (18–45 years) males and females from the local area. Recruitment will proceed on a rolling basis until the adequate sample size is reached. Emphasis will be placed on considering the demands of the study before enrolment to minimise loss to follow-up.

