### Statistical analysis strategy

All statistical analyses will be performed using IBM SPSS Statistics for Windows, v.22.0 (IBM, Armonk, NY, USA). Data will be checked for normal distribution using the Shapiro-Wilk test. The primary endpoint measurement is myo-MPS. Secondary endpoints are leg lean mass (DXA), *rectus femoris* muscle thickness (ultrasound), muscle fibre CSA (immunohistochemistry) and quadriceps muscle strength (isokinetic dynamometry). All measurements will be analysed using a 2-way between and within mixed model ANCOVA with condition (ß-lactoglobulin vs. placebo) as the between-group factor and time period (basal *vs*. prehabilitation *vs.* immobilisation) as within-group factors. Diet and physical activity status will be input as covariates. Where appropriate (i.e. measurements of MPS, leg lean mass, muscle thickness and quadriceps muscle strength), a within-subject control (non-immobilised leg) will be applied to the statistical model when making between group comparisons. The key objective is to compare the effect of the intervention vs. placebo in an unpaired sample. We plan to make three comparisons between the two groups (Δ baseline to immobilisation, Δ prehabilitation to immobilisation, and Δ baseline to prehabilitation for all measurements), disregarding sex as a factor. There is a risk this may introduce type 2 error (rather than type 1 because the randomisation is granular), but we have no reason to anticipate that sex will be a significant confounder. Additional justification for this strategy is because we anticipate that the number of male and female participants will not be equal. The strategy will be to determine from the ANCOVA above whether the intervention is a significant source of variance for each of the primary and secondary endpoint measurements. Bonferroni post hoc testing will be undertaken only if *F* is significant (*P* < 0.05), and there is no variance in homogeneity. The post hoc test will be a *t* test but with an adjustment in the *P* value to accommodate the number of comparisons. The adjustment will be to add a degree of freedom for each of the comparisons. We consider this statistical approach optimal for permitting reliable discovery in a reasonable timeline. Statistical significance will be set an *α*-level of *P* < 0.05.

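### The stated inputs (d = 1.6, 80% power, alpha 0.05) give 8 per group, not 12, and d = 1.6 has no stated link to the β-lactoglobulin versus placebo difference

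*Protocol article*

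**What the plan says.** The Power calculation section of the protocol article takes its effect size from one published study, chosen because it "utilised the same unilateral leg immobilisation protocol, primary endpoint measurement" and enrolled healthy young adults. It reports: "We calculated an effect size (d) of 1.6 for the primary endpoint (MPS) using Eq". In that equation d is the difference between the MPS means of a group 1 and a group 2, divided by their pooled SD. Neither group is identified, and no means or SD are given.

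The effect size then went into G*Power "with power set to 0.8 and significance level" 0.05. The reported result is: "The required sample size was projected to be 12 per group, for a total of 24 participants". The section does not name the test, its sidedness, a dropout inflation or a multiplicity adjustment. Loss to follow-up is addressed only by having volunteers consider the demands of the study before they enrol.

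The Randomisation process section gives 1:1 allocation. The Statistical analysis strategy section says: "The key objective is to compare the effect of the intervention vs. placebo in an unpaired sample". It plans three between-group comparisons of change, from a mixed ANCOVA with diet and physical activity as covariates.

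**The concern.** There are two problems, and they bear on each other.

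First, an effect size of 1.6 is very large, and an unpaired comparison at 80% power should need fewer than 12 per group. If 12 does not come from the printed inputs, a reader cannot tell which effect size, power or allowance the trial was really sized on.

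Second, the source study is matched to this trial on immobilisation, endpoint and population. No supplement or placebo contrast is mentioned. In this trial both arms train and both arms are immobilised, and only the drink differs. The Background says that the authors know of no earlier study of a combined nutrition and exercise prehabilitation programme. An effect size for this trial should describe a difference between the two drinks, and the text does not show that 1.6 does.

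At stake is the reading of a null result. If the true between-arm effect is well below 1.6, a reader who relies on the stated 80% power will take a null result as stronger evidence against the intervention than the design supports.

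**Working it through.** **Inputs from the protocol article.** d = 1.6, power 0.80, alpha 0.05 and 12 per group (Power calculation); 1:1 allocation (Randomisation process); unpaired comparison and three between-group comparisons (Statistical analysis strategy).

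**Assumption.** Two-sided test, because sidedness is not stated. One-sided is also tried.

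**Step 1: normal approximation.** n per group = 2 × (1.960 + 0.842)² / d² = 2 × 7.85 / 2.56 = 6.1, so 7.

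**Step 2: exact calculation for an unpaired t test.** Power is the probability that a noncentral t variable with 2n − 2 degrees of freedom and noncentrality d × √(n/2) falls beyond the critical value.

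| n per group | noncentrality at d = 1.6 | power, two-sided 0.05 |
|---|---|---|
| 7 | 1.6 × √3.5 = 2.99 | 0.785 |
| 8 | 1.6 × √4 = 3.20 | 0.845 |
| 11 | 1.6 × √5.5 = 3.75 | 0.946 |
| 12 | 1.6 × √6 = 3.92 | 0.963 |

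The smallest n that reaches 80% is 8 per group, 16 in total. The plan's 12 per group (24 in total) is not reproduced.

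**Step 3: other readings, with d = 1.6 and power 0.80 kept.**

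| Variant | Required n |
|---|---|
| one-sided 0.05 | 6 per group |
| two-sided 0.025 | 9 per group |
| two-sided 0.05/3 | 10 per group |
| Mann-Whitney, minimum efficiency 0.864 | 9 per group |
| paired t test | 6 in all |

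None of these gives 12 per group.

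**Step 4: what does give 12 per group.** Each route needs something that the section does not state:
- power 0.95 at two-sided 0.05 (achieved power 0.963);
- power 0.90 at two-sided 0.025 (0.926);
- d of about 1.20 at power 0.80;
- 8 per group inflated for about 30% dropout: 8 / 0.70 = 11.4, so 12;
- alpha 0.05/3 plus about 15% attrition: 10 / 0.85 = 11.8, so 12.

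**Step 5: what 12 per group detects.** In an unadjusted two-sample comparison, the smallest d detectable at 80% power is 1.197 at two-sided 0.05. It is 1.414 at 0.05/3, the conventional Bonferroni level for three comparisons.

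For an assumed range of true between-arm effects, at two-sided 0.05:

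| d | power with 12 per group | n per group for 80% |
|---|---|---|
| 1.6 | 0.963 | 8 |
| 1.2 | 0.802 | 12 |
| 1.0 | 0.649 | 17 |
| 0.8 | 0.466 | 26 |
| 0.5 | 0.216 | 64 |

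**The case against.** The strongest reply is that the discrepancy runs in the safe direction. At d = 1.6, 12 per group gives 0.963 power, and still 0.897 at alpha 0.05/3. Nobody is under-recruited at the effect size that the plan names. This stands, and it limits how serious the point is.

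A reader might infer that one of the printed inputs must be wrong. The document does not support that. The test, sidedness, multiplicity and attrition are all unstated, and the last route in Step 4 reaches 12 with every printed input correct. That route is conjecture, because the section presents 12 as the projection from those inputs and mentions no such allowance. It does show that an omitted allowance is as possible as a misprinted input.

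A reader might also infer that 1.6 is the effect of immobilisation itself, and so a ceiling on what a supplement could restore. The document does not show this either. Groups 1 and 2 are unidentified, and the source study cannot be consulted here. The supplement is also taken throughout the training week, so a between-arm difference in change need not be bounded by an immobilisation effect.

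Finally, the detectable differences in Step 5 come from an unadjusted t test, whereas the plan specifies a covariate-adjusted mixed model with a non-immobilised-leg control where appropriate. The residual SD of that model is not known from the document, so these figures are a guide and not the power of the planned analysis.

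**Conclusion.** The point holds in a limited form. As written, 12 per group does not follow from d = 1.6, alpha 0.05 and power 0.80 in an unpaired two-sided t test. The answer is 8 per group, and 12 corresponds to 96% power. Either an input is misreported or an allowance is unstated, and the document does not say which.

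Separately, 1.6 has no stated link to the β-lactoglobulin versus placebo difference that the analysis section makes the key objective. That is a gap in the justification. It is not proof that the wrong contrast was used.

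It also does not follow that the trial is underpowered. That depends on the true between-arm effect, which the document does not establish. Power of 65% at 1.0 SD and 47% at 0.8 SD are values over an assumed range. The result rests on a two-sided test, equal arms, complete data and no covariate adjustment. It is a correction to the reported justification and does not call for a different sample size.

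**What to change.** Keep 24 participants, and in the Power calculation section:

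1. Correct the calculation, or state the input or allowance that gives 12, with the test and its sidedness.
2. Identify groups 1 and 2, give their means and pooled SD, and say which contrast in the source study produced 1.6. If it was not a supplement versus control contrast, say so.
3. Restate what the design detects, for example: *In an unadjusted two-sample comparison of the change in myo-MPS, 12 per arm gives 80% power at two-sided 0.05 for a between-arm difference of about 1.2 SD of the change (about 1.4 SD at alpha 0.05/3 for the three planned comparisons).*
4. Optionally, show power at smaller effects (65% at 1.0 SD, 47% at 0.8 SD), labelled as an assumed range and without describing 1.6 as the immobilisation effect or as an upper limit.

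The cost is wording only. The drawback is that the stated sensitivity becomes less favourable than the present text suggests.

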### Experimental protocol

A SPIRIT figure that details the time points for assessment and intervention is displayed in Fig. 2, and the accompanying SPIRIT checklist is found in Additional file 1.

**Fig. 2 Fig2:**
[figure not shown]
SPIRIT figure showing an overview of the assessment schedule at baseline and follow-up in the study

#### Familiarisation

After informed consent has been obtained, participants will visit the Exercise Physiology laboratory at King’s College London 4 days prior to beginning the prehabilitation period to undertake a familiarisation session. After consent has been received, participants will provide a baseline blood and saliva sample. Next, measurements of height and body weight will be obtained, and participants will be provided with an initial D_2_O bolus to consume in the laboratory (see Stable isotopic tracer methodology section for more information). Participants will be familiarised with knee extensor and knee flexor maximal voluntary contractions and the twitch interpolation protocol to assess levels of voluntary activation for the measurement of isometric strength on an isokinetic dynamometer. For this test, with the leg fixed at 90° of flexion, participants will be asked to perform 3 maximal effort quadriceps and hamstring contractions, each held for 3 s, to determine isometric strength. Prior to each quadriceps contraction, the quadriceps muscle will be electrically stimulated to elicit a maximal twitch. The twitch will be delivered during the maximal contractions at all levels of voluntary activation to be assessed via the twitch interpolation technique. Participants also will be familiarised with the isokinetic dynamometry protocol, which involves maximal quadriceps and hamstrings contractions under dynamic conditions. Participants will be asked to contract their muscle to bring their leg from a 90° angle to straight and back again at two different speeds (60°/s and 120°/s).

At this laboratory visit, participants also will complete a one repetition maximum (1RM) assessment for leg press and single leg extension on both legs individually. Once the familiarisation and 1RM assessments have been completed, and 2 h have elapsed, participants will be asked to provide another blood and saliva sample. Finally, participants will be given an activity monitor (Actigraph GT9X) and physical activity questionnaire [7] to take home and wear for 4 days prior to the next laboratory visit (see Diet and physical activity tracking sub-heading). Participants also will be provided daily top-up boluses of D_2_O to consume over the 16-day period and be provided with tubes to obtain daily saliva samples throughout the trial period.

#### Baseline period

On the morning of day 4 (i.e. following 1 day of familiarisation and 3 days of ‘baseline’), participants will undergo an ultrasound of the *rectus femoris* for measurement of muscle thickness and then be assessed for strength using isokinetic dynamometry. Finally, a muscle biopsy will be obtained from the *vastus lateralis* of one leg under local anaesthesia with the participant fasted. This involves a small piece of muscle tissue being extracted (see the ‘Muscle biopsies’ section) and allows for the measurement of integrated MPS over the baseline period.

#### Prehabilitation period

Days 4–11 will represent the ‘prehabilitation period’ and consist of a complex intervention that combines resistance exercise training with nutritional supplementation. The resistance training programme has been modified from the protocol described by Smeuninx et al. [27]. Participants will complete 4 sessions of bilateral resistance exercise training on leg press and leg extension machines during the prehabilitation period. The final bout of resistance exercise will be conducted ≥ 24 h prior to the 5 day immobilisation period. Each session will consist of two warm-up sets at 50% of 1RM, followed by six sets at 75% of their 1RM for both the single leg press and leg extension. Sets will consist of a target 12 repetitions and will be separated by 2 min rest. All training sessions will last ~ 30 min and will be conducted at a time convenient for the participant.

Participants also will receive a milk-based (β-lactoglobulin) or a carbohydrate supplement (dextrose monohydrate) 3 times per day over the prehabilitation and immobilisation periods. In total, the participant will consume 36 drinks over the 12-day period. Lacprodan® BLG-100 Acidic is a pure β-lactoglobulin derived from whey that delivers a unique amino acid profile and 4% more leucine compared to whey protein. The product is manufactured and packaged according to the relevant EU-regulations for food and food ingredients and/or FAO/ WHO Codex Alimentarius to ensure the milk/milk constituents used as raw material originate from healthy cows. The milk used in production is included in monitoring programmes for undesirable substances as required by regulations or HACCP-based risk assessment.

The placebo (dextrose monohydrate) will be modified to match the same flavour, colour and texture of β-lactoglobulin. The dextrose placebo will undergo the same microbiological testing as the β-lactoglobulin to ensure it is safe for consumption. The list of ingredients for dextrose is as follows: dextrose monohydrate, sucralose, citric acid anhydrous, pineapple flavouring (SC894020), lemon flavouring (SBD 213841) and colour (Yellow 410-WS-P). Both products will be stored at room temperature in a cool, dry place. Compliance will be monitored by requesting participants return all empty packaging.

On day 12, participants will undergo the same procedures (ultrasound, isokinetic dynamometry, and muscle biopsy) conducted at ‘Baseline’.

#### Immobilisation period

Days 12–16 represent the ‘immobilisation period’. On day 12, immediately following the muscle biopsy procedure, participants will have one leg immobilised. The chosen leg will be randomly selected such that 50% of participants have their dominant leg immobilised and 50% their non-dominant leg immobilised. Immobilisation will be achieved by fixing a brace around the knee and maintaining 90° of knee flexion for 5 days. A boot will also be placed on the foot to fix the ankle joint at a 90° angle. Participants will be instructed on the use of crutches for ambulation during this period. Anti-tamper tags will be placed on the brace and bootstraps to indicate if the brace/boot has been modified during the immobilisation period. On day 16, the brace will be removed from the leg, a final ultrasound and strength assessment will be conducted, and two more muscle biopsies (one from each leg) will be collected.

### Experimental procedures

#### Stable isotopic tracer methodology

Free-living integrated rates of MPS will be measured using deuterium oxide (D_2_O) tracer methodology [35]. The D_2_O dosing protocol will consist of a loading day and 15 maintenance days. On day 1 of the trial, and having already provided a background saliva sample, participants will consume a loading dose of 70% D_2_O (Sigma-Aldrich, Poole, UK) that is equal to 3 mL/kg body mass with the aim to label the body water pool to ~ 0.3 atom per cent excess (APE). The loading dose will be dispensed into 50 mL doses and consumed at 30 min intervals to reduce risk of nausea and light-headedness associated with disrupted inner ear equilibrium. Body water enrichment will be maintained in a steady state using daily top-ups of D_2_O based on an 8% per day decay rate. Participants will be instructed to provide a daily saliva sample upon waking, followed by consumption of the D_2_O maintenance dose. The study team will filter the heavy water through a 0.22-μm sterile filter before aliquoting the participant specific volumes into sterile bottles.

#### Muscle biopsies

A total of 4 biopsies per participant will be collected from the *vastus lateralis*. Participants will rest in a semi-supine position whilst a 3–5 mm skin incision is made under local anaesthetic (2% lidocaine) using a surgical blade. The percutaneous needle biopsy technique with applied suction [3] will then be used to obtain 300–400 mg of wet muscle tissue from this site with participants in an overnight (> 10 h) fasted state. The skin will be closed with steri-strips and a waterproof dressing applied to keep the site clean. Muscle biopsies will be conducted on 3 laboratory visits. At baseline, and on day 12, a single biopsy will be obtained from the leg randomly assigned for immobilisation in the leg brace and boot. Biopsy 2 will be conducted > 1 cm proximal to biopsy 1. On day 16 (end of immobilisation period), muscle biopsies will be collected from both immobilised and control legs. Tissue will be immediately snap frozen in liquid nitrogen before all tissue will be transferred to the −80 freezer for storage until further analysis of integrated free-living rates of MPS Wilkinson et al. [35] and static markers of muscle protein breakdown [22]. Approximately 50 mg of muscle tissue will be separated to be mounted for histological analysis, which will not be immediately snap frozen. Fibre orientation of this tissue sample will be assessed using a stereomicroscope before mounting on cork with optimal cutting temperature compound with fibres oriented in the transverse plane. These blocks will be immediately frozen in dry ice cooled isopentane and stored at –80 °C until analysis. A cryostat chilled to –20 °C will be used to cut 10 μm serial sections of these histology blocks, which will be used for ATPase and fluorescence immunohistochemistry staining. All muscle, blood and saliva samples will be logged in eLabJournal.

